### Recruitment and sample size calculation

#### Subproject 1 (quantitative cross-sectional survey with mental health service users)

Focusing on people in psychiatric treatment allows us to survey a representative sample of a defined population. This group represents those with immediate access to therapeutic interventions, and therefore to potentially address experiences of violence. A sufficiently large sample is targeted to enable adequate analyses of different context factors. The sample size of n=500 is chosen to enable the most precise estimation possible of the prevalence of violence experiences.

For statistical power analysis regarding the sample size in subproject one, considering the overall exploratory nature of this study, the variety and theoretical parity of the variables of interest (no primary predictor), and the scarcity of published data that could guide a strict *a priori* power analysis, we liberally set the sample size to 500 or 100 per clinic, respectively. This sample size is sufficient to detect group differences of medium to large effect sizes with a maximum error rate of 5% for both Type I (alpha) and Type II (beta) errors. We illustrate this with the analysis of clinic-level effects using G*Power 3.1.9.7 (36). Based on 500 data points, global parametric comparisons for independent groups can detect site effects on metric variables such as respondent’s age down to f=0.20 with a power of at least 95% (one-way ANOVA with fixed effects, 5 equally-sized groups). This corresponds to site effects on ordinal (e.g. socioeconomic status), nominal (e.g. marital status), or binary variables (e.g. gender) of w≥0.20 (Chi^2^-distribution based tests, df=4). For comparison, a previous study by Johnson et al. (2015) (37) found only a marginal effect of gender on participant status as victim, perpetrator or victim/perpetrator compared to people who did not experience violence (w=0.06, p<0.01). However, comparability of this study’s sample with our target population is strongly limited, as men and people with schizophrenia were overrepresented (59.8% and 63.4%, respectively). For our study, we expect considerably more women than men in psychotherapeutic services (38) and lower rates of schizophrenia, given a prevalence rate of less than 1% in Germany (27).

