Participants will be recruited at the following cooperating hospitals: Clinic and Polyclinic for Psychiatry and Psychotherapy, University Hospital of Leipzig (urban area) (n=100); “Helios Park” - Hospital Leipzig (urban area) (n=100); District Hospital Guenzburg (small town/rural area) (n=100); Specialized Hospital Bethanien Hochweitzschen (rural area) (n=100); Helios Hanseatic Hospital Stralsund (rural area) (n=100). Since violence is a taboo topic, we expect that many people may not want to participate in our study. In order to still obtain a sufficiently large sample size to calculate the aforementioned statistical parameters, we have additionally collaborated with the following two clinics: The Clinic for Psychosomatic Medicine and Psychotherapy at the University Hospital Ulm (urban area). Further, we cooperate with the Clinic for Psychiatry, Psychotherapy and Psychosomatics, Saxon Hospital Altscherbitz, Germany (outskirt of Leipzig). A cooperation has been requested with the Clinic for Psychiatry and Psychosomatics at the District Hospital and the University of Augsburg (urban area).

On a specified key date, the project staff will approach all patients who are receiving partial or full inpatient treatment. For practical reasons, different key dates will be chosen for various treatment units (wards, outpatient clinics). Recruitment will continue in each clinic until the target sample size is reached. Inclusion criteria were legal age (18 years) and German language skills. Exclusion criteria were dementia, intellectual impairment, current psychotic symptoms, and if the person was in isolation or fixation. All patients that meet the inclusion criteria and don’t need to be excluded for above mentioned reasons will be asked if they would agree to fill out the questionnaire. They will be handed the participants information and fill out informed consent (see section “Ethics”).

Furthermore, we will recruit a general population sample (n=1000) through an online survey conducted by USUMA.

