### Data analysis

#### Statistical methods

For subproject 1 and subproject 3, we will describe the type, frequency and context of experienced and exerted violence and compare groups by t-test and ANOVAs. Associations will be analyzed by regression and correlation models (60). Further, we consider multilevel models to analyze group-specific association of varying variables with experienced and exerted violence (61, 62). To assess the psychometric characteristics of new developed and translated questionnaires, descriptive analyses and factor analysis will be conducted (60). Finally, we will interpret the qualitative and quantitative data in conjunction and present the results integratively using joint displays (34, 63).

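### Patients are recruited by treatment unit within a few clinics, but the power figure and the named tests for the patient survey assume independent patients

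*Protocol article*

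**What the plan says.** In the Protocol article, Recruitment and sample size calculation, Subproject 1, the reason given for the sample size is precision: "The sample size of n=500 is chosen to enable the most precise estimation possible of the prevalence of violence experiences". No half-width, assumed prevalence or design effect follows. The number itself is a choice: "we liberally set the sample size to 500 or 100 per clinic, respectively". The section says this suffices for medium to large group differences "with a maximum error rate of 5% for both Type I (alpha) and Type II (beta) errors", and illustrates it with clinic effects. The design "can detect site effects on metric variables such as respondent’s age down to f=0.20 with a power of at least 95" per cent, from a "one-way ANOVA with fixed effects, 5 equally-sized groups". For categorical data the counterpart is "binary variables (e.g. gender) of w≥0.20", with 4 degrees of freedom.

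The same section describes recruitment. Staff approach all eligible patients on a key date, and "different key dates will be chosen for various treatment units (wards, outpatient clinics". Five clinics have a target of 100 each, two more were added, and one has been asked. The abstract says seven.

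Data analysis, Statistical methods, names t-tests and ANOVAs for group comparisons and regression and correlation models for associations. It then adds: "we consider multilevel models to analyze group-specific association of varying variables with experienced and exerted violence". The level of these models is not named. The Outcomes section makes the primary outcome of subproject 1 the frequency of violence experiences compared with the general population.

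**The concern.** Patients treated on one ward tend to be alike in diagnosis, severity, age and setting, so their answers on violence may be correlated. Recruitment goes through such units, but neither the sample-size illustration nor the named tests allow for correlation within them. The one sentence that could do so is not a commitment. It is also aimed at associations, and leaves out the prevalence estimate and the comparison with the 1000 population respondents.

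At stake is the stated uncertainty of the primary outcome, not the point estimate. With any positive ward ICC, an unadjusted test against the population sample rejects too often, and a simple binomial interval covers less than its nominal level. The stated power has little margin to absorb even a small design effect.

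**Working it through.** **Inputs from the protocol article.** N = 500; 5 clinics of 100; alpha 0.05; f = 0.20; w = 0.20 with 4 df; population sample 1000.

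**Inputs assumed, because the documents give none.** 10 patients per ward (about 50 wards); ward ICC 0.01 to 0.10; prevalence 50% for the half-width; 30% versus 20% for the population contrast.

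**1. The plan's own figure.** Noncentrality = N × f² = 500 × 0.04 = 20.
- Noncentral F with 4 and 495 df: power 96.2%.
- Noncentral chi-square with 4 df: power 96.4%.

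The stated minimum of 95% reproduces under independence. About 470 (F) or 465 (chi-square) independent observations are needed for 95%, so a design effect above about 500/470 = 1.06 or 500/465 = 1.08 takes power below it. Separately from clustering, 500 patients in seven equal clinics give 93.7% for the ANOVA.

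**2. Ward clustering.** Design effect DE = 1 + (10 − 1) × ICC; effective n = 500/DE; half-width = 1.96 × √(0.25 × DE/500). Site power is the noncentral F at the effective n.

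| Ward ICC | DE | Effective n | Half-width at 50% (points) | Power, f=0.20, 5 sites |
|---|---|---|---|---|
| 0 | 1.00 | 500 | 4.4 | 96.2% |
| 0.01 | 1.09 | 459 | 4.6 | 94.5% |
| 0.02 | 1.18 | 424 | 4.8 | 92.5% |
| 0.05 | 1.45 | 345 | 5.3 | 85.5% |
| 0.10 | 1.90 | 263 | 6.0 | 73.2% |

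These are powers of a test that allows for wards.

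**3. Unadjusted test of patients against population.** Only the patient arm is clustered. Under no difference, the true variance divided by the variance assumed is (DE/500 + 1/1000)/(1/500 + 1/1000) = (2 × DE + 1)/3. The actual two-sided error rate is P(|Z| > 1.96/√ratio).
- ICC 0.02: ratio 1.12, 1.96/√1.12 = 1.85, error 6.4%.
- ICC 0.05: ratio 1.30, 1.96/√1.30 = 1.72, error 8.6%.
- ICC 0.10: ratio 1.60, 1.96/√1.60 = 1.55, error 12.1%.

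**4. Power of that contrast when wards are allowed for.** For 30% versus 20%, z = 0.10/√(0.21 × DE/500 + 0.16/1000) − 1.96.
- DE 1.00: z = 2.19, power 99%.
- DE 1.18: z = 1.95, power 97%.
- DE 1.45: z = 1.65, power 95%.
- DE 1.90: z = 1.27, power 90%.

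**The case against.** Several points on the other side carry weight.

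- **No interval is stated.** A reader might infer that the published prevalence intervals will be too narrow. The article gives no interval, half-width or interval method, and an article may leave that to the full plan. What remains is conditional: uncertainty is understated if simple binomial intervals and the named tests are used unadjusted.
- **The power figure concerns differences between clinics.** A reader might infer that clustering by clinic inflates it. Clinic is the tested factor there, so it does not. Only correlation within wards inside clinics matters, and the figure is offered as an illustration in a study that calls itself exploratory.
- **Clinic-level design effects look dramatic.** With 100 per clinic, an assumed ICC of 0.01 to 0.02 gives DE = 1 + 99 × ICC = 1.99 to 2.98 and half-widths of 6.2 to 7.6 points. These apply only if results are generalised beyond these clinics. The clinics are named sites with fixed targets, and treated as fixed strata they add no such inflation.
- **Key dates differ by unit for practical reasons.** The text does not say that wards are drawn as a sample, and where a clinic is covered completely the argument weakens. However, recruitment stops at a target number, so complete coverage is not assured.
- **Shared violent incidents on a ward** might be suspected as a source of correlation. The text does not support this; the questionnaire covers past-year and lifetime experiences in general.
- **The main conclusion is probably safe.** Step 4 shows a modest loss of power, and the Introduction cites a five-fold odds for physical violence.

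The core stands. The article does name its tests and does state a power figure. Both assume independence, the recruitment described does not support that assumption, and nothing firm covers the primary outcome.

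**Conclusion.** The point holds as a limited one. The power illustration and the named tests make no allowance for recruitment by treatment unit, and the multilevel models under consideration do not reach the primary prevalence or the population contrast. At 10 patients per ward and ICC 0.02 to 0.10:

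- the half-width at 50% prevalence is 4.8 to 6.0 points rather than 4.4;
- the unadjusted population contrast has a type I error of about 6% to 12% rather than 5%;
- site-effect power is 92.5% to 73.2% rather than 96.2%.

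All of these rest on an assumed ward size and ICC, and at ICC near zero the problem disappears. The stated power is not an arithmetic error: it is correct for independent observations in five equal clinics. Its margin is so thin that 10 per ward at ICC 0.01 already gives 94.5%.

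**What to change.** 1. Use treatment unit as the clustering unit for the prevalence confidence interval and for the comparison with the population sample, with cluster-robust standard errors and each population respondent as a cluster of one. About 50 wards would support this; five to eight clinics would not.
2. Enter clinic as a fixed effect in models within the patient sample.
3. Say that the 95% power figure holds only for independent observations in five equal clinics, or restate it with an assumed design effect.

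The article does not say whether treatment unit is recorded. If it is, only analysis wording changes. If it is not, it should be recorded from now on; for patients already enrolled (250 at submission) it should be reconstructed from clinic and key date where possible, which may not succeed for all. The statistical price is somewhat wider intervals and a less favourable stated power.

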**Methods:**

In a mixed-method study incorporating a quantitative survey and qualitative instruments, we investigate the prevalence of violence, including both victimization and perpetration, among people with SMI. Our study includes the following: (1) In a sample (n=500) of people with SMI, treated in inpatient and outpatient mental health settings, we will investigate the prevalence of victimization and violent behavior, (self-)stigmatization, and barriers for disclosure of experiences of violence within mental health settings. Data will be obtained from samples at seven psychiatric hospitals with mandatory care on a fixed day. For comparisons with the general population, we use an online sample (n=1000). (2) Based on this, we conduct qualitative interviews with a subsample of people with SMI (n=30) who reported experiences of violence. Using biographic-narrative interviews, we focus on the biographical and socio-cultural context (3). In addition, we use qualitative and quantitative measures to investigate mental health professionals’ experiences, institutional factors, and strategies to deal with mental health service users’ violence experiences.

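### The 95% power illustration assumes five equal clinics, while the article describes seven with an eighth requested; at a total of 500 the stated floor is then narrowly missed

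*Protocol article*

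**What the plan says.** All statements are in the Protocol article.

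- **Recruitment and sample size calculation, Subproject 1, power text.** The total and the clinic size are fixed together: "we liberally set the sample size to 500 or 100 per clinic, respectively". The sample is said to suffice for medium to large group differences "with a maximum error rate of 5% for both Type I (alpha) and Type II (beta) errors". This is illustrated with clinic-level effects on metric variables, for which f=0.20 is named as the smallest detectable effect. The power and the test attached to it are: "with a power of at least 95% (one-way ANOVA with fixed effects, 5 equally-sized groups"). The categorical counterpart is given as site effects "of w≥0.20 (Chi^2^-distribution based tests, df=4").
- **Same section, recruitment text.** Five hospitals are listed with n=100 each. Because refusals are expected, the text continues: "we have additionally collaborated with the following two clinics", naming two more without numbers. It then says: "A cooperation has been requested with the Clinic for Psychiatry and Psychosomatics", again without a number.
- **Abstract, Methods.** The total is n=500 and the number of sites is seven: "Data will be obtained from samples at seven psychiatric hospitals with mandatory care on a fixed day".

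**The concern.** The five listed hospitals at 100 each already make 5 × 100 = 500. The text does not say how the added clinics relate to that total, and there are three readings:

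- They count towards 500. Then the five cannot all reach 100, and there are more than five groups.
- All five reach 100. Then the added clinics contribute nothing within 500.
- They recruit on top of five full clinics. Then the total is not 500.

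No reading fits the abstract, the power text and the recruitment text together. The power figure therefore belongs to a site structure that the article no longer describes.

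This matters because the site calculation is the only quantified support for the 5% Type II error statement. The other rationale for 500, precision of the prevalence estimate, carries no figure. With the total held fixed, each extra site adds a degree of freedom to the global test and lowers its power at the same f or w.

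**Working it through.** **Inputs from the power text.** N=500, alpha=0.05, target power 95%, f=0.20 (one-way fixed-effects ANOVA, 5 equal groups) and w=0.20 (chi-square, df=4). **Number of clinics k.** 5 in the power text, 7 in the abstract, and 8 if the requested clinic joins.

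**Formulas.**
- ANOVA: noncentral F with df1 = k − 1, df2 = N − k and noncentrality λ = N·f². Power is the probability of exceeding the central 95% point of F.
- Chi-square, binary variable by clinic: noncentral chi-square with df = k − 1 and λ = N·w².
- Here λ = 500 × 0.20² = 20 in both cases, whatever k is. Only the degrees of freedom change.

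**Step 1: reproduce the plan's figure (k=5).** ANOVA with df 4 and 495 gives 96.2%. Chi-square with df 4 gives 96.4%. Both satisfy the stated floor. The smallest N that still gives 95% is 470 (ANOVA) or 465 (chi-square).

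**Step 2: same total, number of clinics as described elsewhere.**

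| Clinics | ANOVA df | Power at f=0.20 | Chi-square df | Power at w=0.20 |
|---|---|---|---|---|
| 5 | 4, 495 | 96.2% | 4 | 96.4% |
| 7 | 6, 493 | 93.7% | 6 | 94.0% |
| 8 | 7, 492 | 92.4% | 7 | 92.8% |

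Shortfall against 95%, in percentage points:
- Seven clinics: 95 − 93.7 = 1.3 and 95 − 94.0 = 1.0.
- Eight clinics: 95 − 92.4 = 2.6 and 95 − 92.8 = 2.2.

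As Type II error, this is about 6% with seven clinics and 7% to 8% with eight, against the stated maximum of 5%.

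**Step 3: smallest effect with 95% power at N=500.**

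| Clinics | f | w (binary variable) |
|---|---|---|
| 5 | 0.194 | 0.193 |
| 7 | 0.206 | 0.204 |
| 8 | 0.210 | 0.209 |

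**Step 4: total needed for 95% at 0.20.** Seven equal clinics need 528 (ANOVA) or 522 (chi-square). Eight need 554 or 546.

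**Step 5: the broader claim.** At f=0.25, taken here as a conventional medium effect, N=500 gives 99.5% with seven clinics and 99.3% with eight.

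**The case against.** The case against is substantial, and most of it stands.

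- **The number is correct on its printed inputs.** The five-group condition stands beside it, so this is not an arithmetic error.
- **A shortfall is not certain.** The added clinics are presented as a reserve against refusals, and no total or split over seven is fixed. If the five clinics fill, the illustration holds as printed. If recruitment runs past 500 to 528 over seven equal clinics, 95% is restored.
- **The effect is small.** The detectable f moves from 0.194 to 0.206 with seven clinics, and the detectable w of 0.204 still rounds to the printed 0.20.
- **The calculation is offered as an illustration.** The study is exploratory with no primary predictor, and site differences in age or gender are not the primary outcome.

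What remains is that the article gives a floor, not an approximate value. At the only total it states, spread over the seven hospitals it counts, that floor does not hold.

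Two stronger readings are tempting, and the document supports neither. A reader might infer that 500 is too small for the study's aims; step 5 shows that the statement about medium to large effects survives. A reader might also infer that unequal clinic sizes cause a far larger loss. If f is defined with size-weighted variance, λ = N·f² stays at 20 for any split, so inequality alone costs nothing. Larger losses appear only if the clinic means are held fixed and a split is assumed, and the article gives no split over seven clinics.

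**Conclusion.** The point holds as a minor inconsistency with a small numerical consequence. The power illustration is right for five equal clinics of 100, but the abstract and recruitment text describe seven clinics, with an eighth requested and no numbers for the added ones. At N=500 the stated 95% floor is missed by 1.0 to 1.3 percentage points with seven clinics and by 2.2 to 2.6 with eight. The result assumes a final total of 500, all clinics entering the global test, f defined with size-weighted variance (or equal clinics), and a binary variable for the chi-square figures. It does not show that the sample is inadequate.

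**What to change.** 1. Make the abstract, the power text and the recruitment text agree on the number of clinics. Give the planned number for each, including the added ones, and say whether these count towards 500 or come on top.
2. Then do one of the following:
   - Restate the illustration for the clinics actually used. For seven clinics and N=500 this is about 94% power at f=0.20 and w=0.20, or 95% at f of about 0.21 and w of about 0.204 (binary variable, df=6). For eight it is 92.4% and 92.8% at 0.20, or 95% at f=0.210 and w=0.209 (df=7).
   - Keep the present figures and state that they refer to the initial five-clinic plan.

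The cost is a short recalculation and a few sentences. The restated figure is slightly less favourable. Neither the design nor the target of 500 has to change.

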### Data collection and study instruments

#### Subproject 1 (quantitative cross-sectional survey with mental health service users)

Study participants complete the questionnaires on a tablet or using paper-pencil in the clinic. Study staff are available for inquiries. Following a participatory approach, the questionnaire was tested and reviewed in collaboration with peer researchers. Data are collected and managed using REDCap electronic data capture tools hosted at Leipzig University. REDCap (Research Electronic Data Capture) is a secure, web-based software platform designed to support data capture for research studies, providing 1) an intuitive interface for validated data capture; 2) audit trails for tracking data manipulation and export procedures; 3) automated export procedures for seamless data downloads to common statistical packages; and 4) procedures for data integration and interoperability with external sources (39). We will use the following instruments:

The Patient Health Questionnaire (PHQ-D) (40) to assess impairments due to physical and psychological symptoms.Psychiatric and psychotherapeutic hospitalization and treatment experiences as well as diagnoses and symptoms are queried.Substance use is assessed using short forms of AUDIT (41) and DUDIT (42).The German version of the Self-Stigma of Mental Illness Scale (SSMI-SF) (43, 44).One item to assess the general satisfaction with life (45).ISEL-12 (46) to measure social support, and additional items designed with participatory researchers to assess other resources.Questions on sociodemographic characteristics: age, nationality, socioeconomic status (47, 48), sex and gender (similar to 49), family status, sexual orientation (similar to 50, 51), and experienced discrimination.Social desirability is assessed using the Social Desirability Gamma Scale (52).Experiences of violence: a survey on the type, frequency, and context of violence (violence as well as victimization experiences during the last year and over the lifetime), compiled in accordance with (53–55).

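### The detectable site effect w≥0.20 with df=4 does not hold for nominal variables with three or more categories: power there is below the 95% it is equated with (minor)

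*Protocol article*

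**What the plan says.** The statement is in the protocol article under Recruitment and sample size calculation, Subproject 1. On the total, the authors write that "we liberally set the sample size to 500 or 100 per clinic, respectively". They consider this enough for effects of at least medium size "with a maximum error rate of 5% for both Type I (alpha) and Type II (beta) errors", and illustrate it with comparisons between clinics.

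For metric variables, effects are said to be detectable "down to f=0.20 with a power of at least 95% (one-way ANOVA with fixed effects, 5 equally-sized groups"). The next sentence carries this over to categorical variables: "This corresponds to site effects on ordinal (e.g. socioeconomic status"), "nominal (e.g. marital status), or binary variables (e.g. gender) of w≥0.20 (Chi^2^-distribution based tests, df=4"). One effect size and one df therefore serve three types of variable.

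The number of marital-status categories is not given. The instrument list under Data collection and study instruments, Subproject 1, says only "family status, sexual orientation (similar to 50, 51), and experienced discrimination".

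**The concern.** The degrees of freedom of a chi-square test on a contingency table depend on the number of clinics and on the number of categories. With five clinics, df=4 means exactly two categories. The sentence names nominal variables as a class separate from binary ones, so its nominal example must have at least three categories, and df=4 cannot apply to it.

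For a fixed sample size and a fixed w, more degrees of freedom mean less power. The 95% that the sentence inherits from the ANOVA case is therefore too high for nominal variables. What is at stake is the accuracy of the article's stated detectable effect for this one type of variable.

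**Working it through.** **Inputs.** From the sample size section: N=500, five equal clinics, alpha 0.05, target power 0.95, f=0.20 for metric variables, w=0.20 with df=4 for categorical ones. The number of categories c is not stated. I assume 3 to 5; the separation of nominal from binary implies at least 3.

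**Formulas.**
- ANOVA: noncentral F with λ = f²N, df = 4 and 495.
- Contingency table: noncentral chi-square with λ = w²N and df = (5−1)(c−1). Power is the probability of exceeding the 95th percentile of the central chi-square with the same df.

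**The plan's own figures.**
- ANOVA: λ = 0.20² × 500 = 20, power 96.2%; smallest f for 95% power is 0.194.
- Chi-square, df=4: λ = 20, power 96.4%; smallest w for 95% power is 0.193.

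Both reproduce, so the method matches and the df=4 figure is correct where df=4 applies.

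**Which variables have df=4 over five clinics.**
- Binary: (5−1)(2−1) = 4. Correct.
- Ordinal by a rank test such as Kruskal-Wallis: 5−1 = 4. Correct.
- Nominal with c≥3: 4(c−1) ≥ 8. Not 4.

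**Nominal variables, N=500, alpha 0.05, λ=20 at w=0.20.**

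| Categories (assumed) | df | Power at w=0.20 | Beta | Beta ÷ 5% | w for 95% power | N for 95% power at w=0.20 |
|---|---|---|---|---|---|---|
| 3 | 8 | 91.5% | 8.5% | 1.7 | 0.213 | 569 |
| 4 | 12 | 86.6% | 13.4% | 2.7 | 0.227 | 647 |
| 5 | 16 | 81.9% | 18.1% | 3.6 | 0.239 | 712 |

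The last column only shows the size of the gap. It is not a proposal to recruit more.

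**The broader claim.** The article does not define a medium effect. Taking the conventional w=0.30 as an assumption, λ = 0.30² × 500 = 45, and power is 99.97% (df=8), 99.9% (df=12) and 99.8% (df=16). The claim survives for every category count considered.

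**The case against.** The strongest reply is that little depends on this sentence. The article calls the study exploratory, sets N liberally, presents the clinic comparison as an illustration, and gives precision of the prevalence estimate as the reason for 500. The primary outcome is the frequency of violence compared with the general population, not marital status by clinic. The 5% limit on beta is attached to medium and larger effects, not to w=0.20; the 95% reaches w=0.20 only because the sentence presents the two as corresponding. If marital status were dichotomised, df=4 would be right. With three categories the detectable effect moves only from 0.20 to 0.213.

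All of this stands as a limit on importance. It does not make df=4 right for a nominal variable: the article does not say that marital status will be dichotomised, and it lists nominal apart from binary.

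A reader might infer more than the document supports:
- **That 500 is too few.** It was not derived from this calculation, and the claim about medium or larger effects holds.
- **That real site differences will be missed and the clinics treated as comparable.** The Statistical methods section plans description, t-tests and ANOVAs, regression and correlation, and considers multilevel models. No decision on pooling or adjustment depends on a non-significant test of marital status by clinic.
- **That the whole sentence is wrong.** The binary case is correct, and so is the ordinal case under a rank test.
- **That the additional clinics make matters worse.** The calculation is explicitly for five equal groups. How many clinics will be compared is a separate question.

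**Conclusion.** The point holds, confined to nominal variables. With three or more categories over five clinics, df=4 is the wrong value, and the 95% power equated with w≥0.20 is not reached. This conclusion needs no assumption about the exact number of categories, since every count above two gives less than 95%.

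The size of the shortfall does depend on that number. Under the assumed 3 to 5 categories it runs from 3.5 percentage points (95 − 91.5) to 13.1 (95 − 81.9). In terms of detectable effect the shift is modest, and the result stays below w=0.30. Severity is minor: an illustrative figure is misstated for one type of variable, with no consequence for the sample size, the primary outcome or the planned analyses.

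**What to change.** Restrict w≥0.20 with df=4 to binary variables and to rank tests of ordinal variables. For nominal variables, state the number of categories, use df = (clinics − 1) × (categories − 1), and give the matching w. For example: marital status in four categories over five clinics, df=12, w≥0.23 with 95% power (about 87% at w=0.20). If marital status is to be dichotomised for this comparison, saying so would also resolve the point.

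The cost is one sentence in the sample size section. The stated detectable effect for nominal variables becomes slightly less favourable. No additional participants and no change to the analysis are needed.
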